### Outcomes

Aspects of feasibility will be assessed using metrics derived from the following: (1) Recruitment rate: the effectiveness of recruitment strategies will be determined by the percentage of eligible residents who agree to participate, with the response rate calculated as the number recruited compared with the number approached. (2) Retention rate: Determine the proportion of participants who remain enrolled from the start to the end of the study. Document and categorise reasons for dropout, if available. (3) Attendance rate: Calculating the ratio of sessions attended by each participant to the total number of sessions offered, often expressed as a percentage. (4) Scale completion rate (specifically for older people): Assess the completeness of scale responses by calculating the proportion of older people who fully complete the scales and noting the number of missing items per scale. Four scales will be used, including the modified Chinese version of the Geriatric Depression Scale 11-item version (CGDS-11) for measuring depression, the Chinese version of the Geriatric Anxiety Inventory (GAI-CV) for assessing anxiety, the Chinese version of the De Jong Gierveld Loneliness Scale (DJGLS) for gauging loneliness and the Chinese versions of the 12-item Short Form Health Survey (SF-12) for evaluating quality of life. All four scales have existing Chinese and English versions available.

The CGDS-11 is derived from the Chinese version of GDS-15, with questions 2, 8, 9 and 13 based on GDS-15.^39^ It is applied in a variety of healthcare and research contexts and has become known as an essential tool to assess the mental health of older people. The items of GDS use a simple yes/no response format, which is particularly preferred by older people. The Cronbach’s alpha coefficient for the CGDS-11 is 0.763, and the test–retest reliability is 0.712.^39^

The GAI-CV has strong psychological qualities, making them reliable in identifying anxiety in older people.^40^,^42^ Its predictive and concurrent validity have been verified.^43 44^ The GAI-CV shows strong reliability (Cronbach’s α=0.937) and a fitting three-factor model (Comparative Fit Index [CFI]=0.891, Root Mean Square Error of Approximation [RMSEA]=0.084), making it an effective tool for measuring anxiety among Chinese older people.^45^

The DJGLS is a reliable instrument for assessing loneliness, available in 11-item and 6-item versions that measure both emotional and social loneliness.^46^ With a Cronbach’s alpha of 0.820 for the overall scale and scores of 0.792 and 0.737 for the social and emotional loneliness subdimensions, respectively, the Chinese version of the DJGLS shows high reliability and validity, making it highly suitable for assessing loneliness among Chinese older people.^47^

The SF-12 is a shorter version of the SF-36 designed to effectively assess an individual’s quality of life.^48^ The SF-12 contains 12 questions spanning 8 health domains, adopting both Likert scales and binary choices like ‘yes’ or ‘no’.^49^ Numerous studies have shown that the Chinese version of the SF-12 is a viable and reliable instrument for assessing the health and quality of life of the Chinese elderly population.^50^,^52^

Both acceptability and feasibility will be evaluated through semistructured and focus group interviews, focusing on participants’ (residents, young people and staff) satisfaction with the IE intervention, their willingness to continue with or recommend the programme, and their experiences and perceptions of the IE intervention and suggestions for improvement.

Purposive sampling^53^ will be used to select 14–20 older people for qualitative individual interviews based on their interest in participating. This recruitment strategy emphasises selecting participants who are willing to engage in the interview process, thereby ensuring that the data collected are both rich and insightful. The interviews are designed to delve deeply into participants' experiences and perceptions with the IE intervention, with a special focus on its acceptability. Key areas of inquiry will include satisfaction with the intervention, willingness to continue or recommend, acceptability of the scales and their overall experiences and perceptions.

In addition to individual interviews with residents (older people), the study will involve two separate focus groups. One group will comprise five staff members directly involved in implementing the IE intervention. This group will provide an opportunity to discuss their observations during the intervention, the feasibility and acceptability of implementing it within the facility, and any perceived benefits or challenges. Key discussion topics will include satisfaction with the intervention, observed intergenerational interactions and suggestions for improvement.

The other group will consist of 7–8 young people who have actively participated in the IE intervention and are willing to take part in the group discussion. This focus group will centre on their experiences of interacting with older people, including what they found rewarding or challenging. Discussions will aim to understand young people’s views on the value of the IE intervention and the intergenerational relationships it fostered. Key areas of inquiry will involve their satisfaction with the programme, willingness to engage in similar future activities, suggestions for future improvement, and perceptions of intergenerational relationships and mutual understanding.

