### Study participants

#### Older people

This feasibility study will recruit 30 older people residing at the study site for the IE study. Eligibility criteria for older people will include: (1) aged 60 years or above; (2) in relatively good physical and mental health, able to perform daily activities with minimal assistance and actively participate in the study without requiring intensive medical or psychological support; (3) able to communicate effectively in either Cantonese or Mandarin, including understanding, responding to questions and engaging in conversations and (4) willing to participate in the IE programme and provided signed informed consent.

Older people will be excluded if they: (1) have medium or severe cognitive impairments, experiencing an acute phase of a chronic disease, have severe physical disabilities (eg, bedbound) or were in the end-of-life period; (2) were unable to communicate effectively in either Cantonese or Mandarin and (3) declined to provide informed consent or expressed unwillingness to engage in the IE programme.

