#### Young people

We will recruit 15 young people aged 15–16 years from a local school near the LTC facility. Eligibility criteria for young participants included: (1) willingness to participate in the IE programme and provision of a signed assent form, with written consent also obtained from a parent or legal guardian; (2) relatively good physical and mental health and (3) ability to communicate effectively in either Cantonese or Mandarin.

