#### LTC facility staff

Five staff will be recruited. Eligibility criteria for staff will include: (1) currently employed at the LTC facility and (2) willingness to assist with the IE programme and after eliciting informed signed consent, participate in a focus group following delivery of the intervention.

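### Older interviewees are selected only on interest and the young people's focus group on active participation, so the acceptability evidence probably under-represents those who left or attended little

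*Protocol article*

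**What the plan says.** All references are to the protocol article.

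- **Older people (Outcomes).** Purposive sampling "will be used to select 14–20 older people for qualitative individual interviews based on their interest in participating". The rationale follows: "This recruitment strategy emphasises selecting participants who are willing to engage in the interview process". No criterion based on attendance, retention or range of views is stated. The pool is fixed under Older people: "This feasibility study will recruit 30 older people residing at the study site".
- **Young people (Outcomes).** The focus group consists of "7–8 young people who have actively participated in the IE intervention and are willing to take part in the group discussion". The pool is fixed under Young people: "We will recruit 15 young people aged 15–16 years".
- **Staff (Outcomes; LTC facility staff).** "One group will comprise five staff members directly involved in implementing the IE intervention". Since "Five staff will be recruited", every staff participant takes part.
- **Role of these data.** The Introduction gives the aim as feasibility and acceptability. Outcomes defines recruitment, retention, attendance and scale completion as feasibility metrics, and assigns acceptability to the interviews and focus groups. Topics include satisfaction and willingness to continue with or recommend the programme.
- **Other relevant data (Outcomes; During the intervention).** Attendance is recorded for each participant at each session, with reasons for absence. Dropout and its timing are recorded, with reasons if the participant offers them.
- **Limitations (Strengths and limitations).** The list names small sample size and short follow-up, but not how interviewees are selected.

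**The concern.** Purposive sampling means choosing people on characteristics that bear on the question. Here the only stated characteristic for older people is interest in being interviewed, which makes it a volunteer sample under another name. For young people the stated characteristic is engagement with the programme, and engagement is closely tied to acceptability itself.

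People who withdrew or came rarely are plausibly those whose answers on satisfaction and willingness to continue differ most from the rest. If they are few or absent in the interviews, the study learns least about acceptability where it most needs to. The planned integration would then set retention and attendance over all participants beside views from a more engaged subset, although the article presents its data sources as able to validate one another. Study entry already requires willingness to join the programme, so selection for interview adds a second volunteer filter.

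**Working it through.** **Step 1. The article's own total.** 30 older people + 15 young people + 5 staff = 50, which agrees with the Sample size section. No alpha, power or bias figure bears on this point.

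**Step 2. Room for selection.** Fraction heard = n/N; number not heard = N − n.

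| Group | N | n | Fraction heard | Not heard |
|---|---|---|---|---|
| Older people | 30 | 14–20 | 46.7%–66.7% | 16–10 |
| Young people | 15 | 7–8 | 46.7%–53.3% | 8–7 |
| Staff | 5 | 5 | 100% | 0 |
| All | 50 | 26–33 | 52%–66% | 24–17 |

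Only in the two participant groups is there a choice of whom to hear, and in both a large part of the group goes unheard.

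**Step 3. The two rules side by side.** The older people's rule contains no engagement condition: a resident who withdrew remains eligible if interested. The young people's rule does contain one. The rules therefore act differently, by under-representation in one group and by exclusion in the other.

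**Step 4. What sampling blind to engagement would give (assumed numbers).** The article gives no dropout or attendance rate, so let D be the number of withdrawers and low attenders. The expected number in the sample is n × D/N. The chance that it contains none is C(N−D, n)/C(N, n).

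*Young people, D = 3 of 15:*
- n = 7: 7 × 3/15 = 1.4 expected; chance of none 12.3%.
- n = 8: 8 × 3/15 = 1.6 expected; chance of none 7.7%.
- Over D = 2 to 5, the expected number runs from 7 × 2/15 = 0.9 to 8 × 5/15 = 2.7.
- Under the written rule, read plainly, the number is 0 whatever D is.

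*Older people, D = 6 of 30:*
- n = 14: 14 × 6/30 = 2.8 expected; chance of none 1.3%.
- n = 20: 20 × 6/30 = 4.0 expected; chance of none 0.04%.
- Over D = 3 to 9, the expected number runs from 14 × 3/30 = 1.4 to 20 × 9/30 = 6.0. At D = 3 the chance of none is 13.8% (n = 14) or 3.0% (n = 20).

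**Step 5. Older people under self-selection (assumed).** Suppose the 6 low engagers are half as likely to be interviewed as the other 24. If p is the chance for the others, then 24p + 6(p/2) = n, so p = n/27, and the expected number of low engagers is 6 × (p/2) = 3n/27. That is 1.6 at n = 14 and 2.2 at n = 20, against 2.8 and 4.0 in step 4. If interest in being interviewed is unrelated to engagement, there is no shortfall.

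Steps 4 and 5 illustrate who would be heard. They do not estimate a bias in acceptability.

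**The case against.** The strongest reply has five parts.

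1. *Every interview sample is limited to the willing.* True, because participation is voluntary, and the proposed change has the same limit. But willingness as a condition of consent differs from willingness as the only selection criterion. The article states the second.
2. *Interest in the interview is not enthusiasm for the programme.* A dissatisfied resident may want to be heard. This stands. A reader might infer that older people who dropped out are barred from interview, but no rule in the article does that. The supportable statement is that nothing provides for including them.
3. *Other data cover those who left.* Reasons for absence are recorded, as are dropout reasons when offered, and staff discuss what they observed, including challenges. This offsets the problem in part. However, the recorded reasons belong to retention and attendance, dropout reasons depend on the person volunteering them, and the staff are involved in delivering the programme. None of these replaces a participant's own account.
4. *Active participation is undefined and may mean only having taken part.* That reading is possible, and on it the exclusion weakens. The plain reading is a condition on engagement, and ambiguity in an entry condition is itself a reason to remove it. That group's agenda does include challenges and suggestions for improvement, but it puts them to those admitted.
5. *A condensed article may leave a sampling grid to the full protocol.* Agreed for the detail. The point here rests on rules the article does state.

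**Conclusion.** The point holds in a limited form. As written, the young people's rule excludes those who stopped or attended little. The older people's rule leaves such people eligible but probably under-represented. Because interviews and focus groups are the main acceptability evidence, the themes are likely to lean favourable, and the stated limitations do not warn the reader of this.

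A reader might go further and infer that acceptability will be overstated by a definite number of percentage points. The document does not support that. The interviews are analysed thematically, no proportion finding the programme acceptable is planned, and no dropout, attendance or satisfaction rates are given from which a bias could be computed. The favourable direction is an inference. It rests on the assumption that low engagement goes with less favourable views and, for older people, with less interest in being interviewed. What the document does fix is the scope: 10–16 of 30 older people and 7–8 of 15 young people are not heard. The study remains sound in its other parts, and this is a cheap improvement worth making.

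**What to change.** Keep the planned numbers of interviews and focus-group places, and change the selection rules:

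- Use the attendance and retention data already recorded as the purposive criteria for older interviewees, and actively invite withdrawers and low attenders.
- Delete active participation as a condition for the young people's focus group, and invite low attenders and withdrawers there too.
- Report how many low attenders and withdrawers were invited in each age group and how many agreed.
- Add the remaining self-selection to the stated limitations.

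The attendance level that counts as low, and any further characteristics used to fill the sample, are for the study team to set in advance.

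The cost is a change of wording and a simple sampling grid, with no extra interviews. The downside is that withdrawers are harder to reach and some will decline. Participation stays voluntary, so part of the selection will remain, but it will be visible in the report.

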### Data collection

#### Before the intervention

Baseline demographic data will be collected from older people, including age, gender, education level, marital status, living support and health conditions. They will also invite to complete four scales: CGDS-11, GAI-CV, DJGLS and SF-12. The entire data collection process takes 35–40 min. For staff and young people, only demographic data will be collected.

#### During the intervention

We will record participant engagement, focusing on two key aspects: retention and attendance rates. Participant dropouts will be recorded, and the specific time of dropout will be noted if applicable. If participants are willing to provide reasons for leaving, these reasons will also be recorded. Also, we will document the attendance of each participant at every session, recording both their presence and the reasons for any absences.

#### After the intervention

In the quantitative component, older people will complete the following four scales as a post-test: CGDS-11, GAI-CV, DJGLS and SF-12. This will be conducted within 7 days after the intervention to assess its immediate feasibility results before potential external effects can have an impact.

In the embedded qualitative component, we will capture valuable insights into the acceptability of the intervention through interviews and focus groups. For older people, semistructured individual interviews will be conducted to explore their experiences, with each interview lasting 30–45 min. For staff and young people, focus groups will be organised, with each session expected to last between 60 and 90 min.

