**Trial registration number:**

ISRCTN14922432.

Strengths and limitations of this studyOur study’s use of both quantitative and qualitative data provides a comprehensive understanding of the feasibility and acceptability of the intergenerational engagement (IE) intervention. This design enables findings from different data sources to validate each other, thereby enhancing the robustness of the study.This study includes older people, young people and long-term care facility staff, providing a holistic view of the IE. This diversity helps in understanding the perspectives and experiences of different age groups and roles within the care setting.The inclusion of a patient and public involvement team, comprising older people, staff, young people and parents, ensured the intervention’s feasibility, accessibility and clarity, enhancing its relevance and applicability by refining the intervention design and recruitment process.As a feasibility study, the sample size is relatively small, which may limit the generalisability of the findings.The follow-up assessment will be conducted within 7 days after the intervention, which may not capture the long-term effects of the IE intervention. Longer follow-up periods would provide more information on the sustained impact of the intervention.

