### Sample size

The total sample size for this feasibility study will be 50 participants, including older people, young people and staff. Feasibility studies assess study practicality rather than intervention effectiveness or association strength, and they frequently do not include thorough power-based sample size analyses.^32 33^ Guidelines for sample sizes in feasibility studies are limited, and existing recommendations vary.^34^ In feasibility studies aimed at determining the standard deviation (SD), participant sample sizes vary; some suggest 30, while others propose a range between 24 and 50.^35^,^37^ In planning the logistics and management of the IE intervention, suggestions from patient and public involvement (PPI) members (staff) have been integral. A key consideration has been the available space in the activity room at the LTC facility. To ensure that IE activities will not be overcrowded or noisy, the feasibility study is limited by the capacity of the activity room to a maximum of 55 people. This limit will ensure ample space for both groups of participants to engage in activities while maintaining an environment conducive to interaction.

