### Data analysis

In the quantitative component, descriptive statistics will be used to summarise the demographic information of participants and to provide an overview of the recruitment rate, retention rate, attendance rate and scale completion rate. This will involve calculating means, SD, frequencies and percentages.^54^ The scale completion rate will be assessed by determining the proportion of scales completed in full by participants. To examine the differences in outcomes before and after the intervention, independent sample t-tests will be employed to compare the change scores from the pretest to the post-test. In the qualitative component, thematic analysis will be used to analyse data collected from both qualitative interviews and focus groups.^55^ The content of interviews with older people and focus groups with staff and young people will be examined to identify themes related to the acceptability of the intervention. Findings from the quantitative and qualitative components will be brought together during interpretation to inform a comprehensive understanding of feasibility and acceptability.

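### Independent-samples t-tests are planned on one uncontrolled cohort; even a paired test would show change, not effect, and the 7-day post-test window does not alter that

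*Protocol article*

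**What the plan says.** Under Older people: "This feasibility study will recruit 30 older people residing at the study site for the IE study". They are the only group given the scales (CGDS-11, GAI-CV, DJGLS and SF-12), once before the programme and once within 7 days after it. The programme runs over 5 weeks (Intervention). The text describes no control or comparison group.

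After the intervention (Data collection) gives the reason for the 7-day limit: "to assess its immediate feasibility results before potential external effects can have an impact".

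Data analysis introduces the tests with the words "To examine the differences in outcomes before and after the intervention" and names independent sample t-tests on the change scores. The Abstract names the same test.

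Two other sections point away from testing. Study design says that the quantitative data will be analysed descriptively to assess feasibility. Sample size says: "Feasibility studies assess study practicality rather than intervention effectiveness or association strength".

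The strengths and limitations list names the small sample and the short follow-up, "which may not capture the long-term effects of the IE intervention". It does not name the lack of a comparator.

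**The concern.** Three problems meet in the same analysis.

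- **The named test does not fit the design.** An independent-samples t-test compares two separate groups. One cohort yields one set of change scores, so there is nothing to compare them with. The test could be run by treating the post and pre scores as two samples, but they come from the same people.
- **Repairing the test does not repair the inference.** A paired test answers whether scores moved. Without a comparator it cannot say why. Other events in the facility, changes in health, retesting, and response to the researcher and staff who facilitate the sessions all act over the same period as the programme.
- **The stated rationale for the window hides this.** It can be read as saying that a prompt post-test keeps external influences out of the comparison. Nothing in the limitations corrects that impression.

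At stake is what the study reports for its four scales. As written, it would give either a P value from a test that cannot be run as named or an interval much wider than the data support. A reader could then attach a P value to the programme that the design cannot attribute to it.

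**Working it through.** **The plan's own figure.** The only sample-size figure is a total: "The total sample size for this feasibility study will be 50 participants, including older people, young people and staff". The groups are 30 older people, 15 young people and 5 staff: 30 + 15 + 5 = 50. It reproduces. No alpha, power, effect size or SD is given, so there is no power calculation to check. The scale analysis rests on n = 30.

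**Timeline.** The pretest comes before the programme, with no window stated. The programme takes 5 weeks. The post-test follows within 7 days. The interval is therefore about 5 to 6 weeks plus any gap before the first session. The 7-day limit governs only the last part of it.

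**Inputs for the precision check**

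- n = 30 (Older people), assuming that all complete both assessments.
- Pre/post correlation r = 0.712. This is the test–retest value that Outcomes gives for the CGDS-11. Using it as the pre/post correlation, and for the other scales, is an assumption, so r = 0.3 to 0.8 is also shown.
- Equal SD before and after, normal data, two-sided 5% level. These are assumptions too.

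**Half-width of the 95% interval, in baseline SD units**

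- Paired: SD of change = √(2(1 − r)) = √(2 × 0.288) = 0.759. Standard error = 0.759/√30 = 0.1386. Half-width = t(0.975; 29) × 0.1386 = 2.045 × 0.1386 = 0.28.
- Post against pre as two samples: half-width = t(0.975; 58) × √(2/30) = 2.002 × 0.2582 = 0.52.

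The two-sample form is wider by a factor of 0.517/0.283 = 1.8. With no true shift it rejects in well under 1% of studies at r = 0.712 (simulation: about 0.06%) rather than the nominal 5%. Its error is therefore towards missing change.

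**What a correct paired test would detect.** Suppose the mean moves by 0.3 SD for any reason. The noncentrality is 0.3/(√(2(1 − r))/√30), on 29 degrees of freedom.

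| r | SD of change | Paired half-width (SD) | Noncentrality | Chance of P < 0.05 |
|---|---|---|---|---|
| 0.3 | 1.183 | 0.44 | 1.389 | 27% |
| 0.5 | 1.000 | 0.37 | 1.643 | 36% |
| 0.712 | 0.759 | 0.28 | 2.165 | 55% |
| 0.8 | 0.632 | 0.24 | 2.598 | 71% |

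For a 0.2 SD shift at r = 0.712 the chance is 29%. Post against pre as two samples would flag the 0.3 SD shift in about 7.5% of studies at r = 0.712 (simulation).

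The 0.3 SD shift is chosen for illustration; the protocol gives no figure for drift. The table shows only that a paired test responds to a moderate shift and does not distinguish its cause.

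**The case against.** The strongest reply is that the study never claims to measure effect. Its aim is feasibility and acceptability, the scales enter Outcomes under the scale completion rate, and Sample size sets effectiveness aside. This stands in part. A reader might infer that a significant change will be reported as benefit, but no section says so. It is a risk that the wording leaves open, not a stated plan. The same passages also count against the tests, because a study that sets effectiveness aside and promises descriptive analysis has little use for a P value on outcome change.

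Second, the window sentence can be read narrowly, as limiting influences between the last session and the measurement. A short window does that, and a paired test is valid as a test of change. Both points stand; only attribution to the programme fails. But the sentence carries no such qualifier, and the feasibility rates themselves need no protection from external effects.

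Third, the 55% does not describe the test as named. It assumes a paired test, a drift with no source in the protocol, full completion and one scale's retest value. This is correct, and the figure is offered only as an illustration with its range.

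Two further inferences are not supported. A seasonal shift is speculation, because no session dates are given. An inflated false-positive rate across four scales does not describe the named test, which is conservative if run as post against pre, and multiplicity for exploratory scales is commonly left to an analysis plan that is not shown.

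**Conclusion.** The point holds as a mismatch between design, named test and stated purpose. The independent-samples test has no second group in the design as described. If forced into post against pre, it gives intervals about 1.8 times too wide at r = 0.712 (0.52 against 0.28 SD). Correcting it to a paired analysis gives a sound estimate of change, but not of effect, and the 7-day window does not change that.

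The conclusion about the test and about attribution needs no numerical assumption. It rests on the text describing no comparator; Figure 1 is not shown. The sizes rest on n = 30 with full completion, equal SDs and the assumed correlation. The 55% (27% to 71%) also rests on the assumed 0.3 SD shift.

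The recruitment, retention, attendance and completion rates and the qualitative strand are unaffected. The documents do not support saying that the study plans to claim benefit, or that its tests as named would produce excess false positives.

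**What to change.** - **Abstract and Data analysis:** replace the independent sample t-tests with the mean within-person change, its SD and its 95% CI for each scale, labelled as estimates for planning a later trial.
- **After the intervention:** reword the rationale to say that the 7-day window limits only influences arising after the last session.
- **Strengths and limitations, and Data analysis:** state that there is no comparator, so pre/post change will not be interpreted as an effect of the intervention.

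The changes are to wording and to one summary table. Design, recruitment and data collection stay as they are. The only loss is P values that could not be attributed to the programme.
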